### Intervention

Residents who meet the sample selection criteria will be recruited. We will interview potential participants and their relatives to explain the purpose of the project. Their cognitive level will be assessed with the C-MMSE, whereas their communication ability will be assessed by two items in the Hong Kong version of the interRAI-HC assessment during participant recruitment. Additionally, their verbal fluency will be assessed by the Modified Fuld Verbal Fluency Test (M-FVFT) [23]. Demographic data, pain-related diagnoses, and medical history will be collected by reviewing participants’ medical records.

#### *Baseline assessment*

Baseline assessment will include the weekly MQS III score and the weekly record of non-pharmacological pain treatments. Participants’ daily use of pain medications will be quantified into the MQS III scores. Other non-pharmacological pain-relieving interventions will also be recorded daily. Both of these records will be collected weekly for the first 4 weeks of the intervention cycle by the designated research assistant (RA). This collection will continue for the 12 weeks of the Protocol implementation in the experimental care homes or during the usual pain management period in the control care homes. In addition, participants’ C-PAINAD scores will be collected by the independent pain observer once a week throughout the 16-week study period. Please refer to the section below for a detailed explanation of the role of the independent pain observer.

#### *Implementation of the Protocol in experimental long-term care homes*

Four 1-hour workshops will be conducted by JL during the first 4 weeks of the intervention cycle. These will aim to ensure that both professional and non-professional care home staff understand and follow the Protocol correctly. Workshop I will introduce pain assessment and management for older people with dementia. Workshops II and III will explain the use of the Protocol for their pain assessment and treatment. The staff will practise pain assessment by C-PAINAD through various pre-developed clinical vignettes. They will also learn to discriminate between various steps of pain treatments based on the pain score. Group discussions will be held after the practice. The staff will be asked to explain their choice of indicators and give reasons for their choice. They will also be asked to explain their subsequent actions in terms of the selection of different stages of pain treatments suggested by the Protocol. Through practice and discussion sessions, the staff should be able to follow the Protocol. Workshop IV is mainly about the implementation of the Protocol. Finally, a test will be conducted to ensure that the staff understand the Protocol. Given that the job nature and educational backgrounds of professional and non-professional caregivers are different, they will attend the workshops separately. The workshops’ contents will be tailored to suit these two groups of staff.

Following the training workshops and after ensuring that all care home staff understand and can follow the Protocol (Table 1), it will be formally incorporated into the care homes’ daily routine.

1. *Pain assessment*: The staff will perform a daily observational pain assessment using the C-PAINAD when participants are undergoing potentially pain-triggering nursing procedures or exercising. Since pain-related behaviors are more likely to be observed when pain is triggered by movement [24], pain may also be exacerbated by the movement that occurs with different types of nursing activities [25-27]. This means that nursing care can potentially trigger pain. Studies have shown that the PAINAD is more sensitive in detecting pain while patients are moving or exercising [28]. The pain assessment suggested in this protocol will be used at least once per day when participants are undergoing potential pain-triggering nursing procedures or exercising. Since most of these nursing procedures are scheduled in the morning shift, the staff will be instructed to perform observational pain assessment at least once per day during the AM shift. They will also be encouraged to re-assess participants’ C-PAINAD scores whenever necessary.

2. *Pain score interpretation and verification*: On the C-PAINAD scale, 0 indicates no pain and 10 indicates severe pain. In this study, C-PAINAD >1 will be considered an indication of pain or discomfort. Pain treatments should then be implemented. The PAINAD was converted into a categorical scale based on items in the 4-point Verbal Rating Scale, in which 0-1 corresponded to no pain; 2-3 to mild pain, and a score of 4 and above would correspond to moderate pain and above [29]. These findings will be used to interpret the C-PAINAD score. However, since none of the pain-related behaviors are specific to pain, verification procedures are needed. First, it is suggested that the staff investigate the possible causes of pain (for example, history of recent injury or pain-related diagnosis). Second, they need to obtain the participant’s self-report if at all possible, by asking simple yes / no pain questions to participants. Whenever necessary, the staff should also collect information from surrogates, direct contact nurses, and so on. If there is no evidence indicating pain, the staff should attempt to interpret the meaning of the behavior in question with the help of others who are familiar with the participant. Additionally, the staff are also required to ensure that participants’ basic needs are met (for example, check whether they are hungry, thirsty, or seeking attention for another reason). If evidence shows that the observed behaviors are highly likely to be caused by pain, staff are required to implement treatment to relieve pain.

3. *Implementation of pain-relieving interventions*: In many circumstances, pain can be alleviated by simply removing or correcting the cause, such as maintaining a proper body alignment while transferring residents with back problems [30]. The Pain-minimizing and Caregiving Guidelines designed by Talerico and her colleagues [31] (Table 2) were therefore adopted in this protocol and will be considered as the first step in pain treatment. The guidelines should be implemented when the C-PAINAD score >1. They aim to make caregivers aware of participants’ behavioral pain expressions during potential pain-triggering nursing procedures. Signs will be placed at bedsides to remind caregivers to take great care while conducting nursing activities. If the interventions in Step 1 fail to decrease a participant’s C-PAINAD scores, Step 2 pain treatment should be initiated. If the C-PAINAD score >4, Step 2 should also be implemented. Step 2 interventions involve both non-pharmacological and pharmacological treatments. The treatment choices at this stage are tailored to the needs of particular participants. In-house physiotherapists, occupational therapists, and nurses-in-charge will be consulted about non-pharmacological treatment. If residents have been prescribed PRN analgesic medications, those medications should be administered. If residents are prescribed regular analgesic medications, these should be administered 30 minutes before the potential pain-triggering nursing procedures. If residents have not been prescribed any analgesics, nurses are advised to discuss the prescription of suitable medications with physicians.

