The Protocol was used to guide the pain management of 30 care home residents with dementia, with at least one pain-related diagnosis, for 8 weeks. Before the implementation, only five residents had been prescribed pain medications. Pain medications administered to the residents were quantified by the Medication Quantification Scale (MQS) [19]. During the study period, the mean MQS score increased from 10 (SD 14.23) at week 1 to 23.41 (SD 10.58) at week 8. The percentage of residents given pain medications increased to 23.33% (n = 7) at week 8. Similarly, only six residents were receiving non-pharmacological interventions at week 1. Towards the end of the study period, 17 residents were receiving non-pharmacological pain-relieving interventions such as hot pads, ice therapy, and massage. The mean pain score of the 30 residents decreased slightly from 2.87 (SD 1.30) at week 1 to 2.57 (SD 1.32) at week 8. Although this study did not show a statistically significant reduction of pain scores, probably due to the small sample size, it did show clinical relevance in improving pain management. Incorporation of this Protocol into the long-term care home’s daily routine encouraged well-organized pain recording for each resident, allowing further comparisons of pain treatment effectiveness. Besides this pilot study, no other study has been conducted to evaluate the effectiveness of similar protocols in improving pain management practice.

The aim of this study is to investigate the extent to which the implementation of the Observational Pain Management Protocol can improve the management of pain for older care home residents with dementia. Based on the findings in our pilot study [18], we hypothesize that the implementation of the Protocol will result in an improvement in pain management for residents with dementia, as manifested in an increased use of both pharmacological and non-pharmacological pain treatments. As a consequence, behavioral pain scores will be lower due to better pain management. The following two research objectives have been derived:

1. To investigate whether a systematic use of the Protocol improves pain management, as manifested by the increased use of pharmacological and non-pharmacological pain treatments for residents with dementia.

2. To investigate whether the use of this Protocol results in lower observational pain scores for residents with dementia.

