#### *Independent pain observer*

The staff in the experimental care homes will be aware of the pain treatment received by the participants. In view of the fact that possible expectancy bias may develop among staff in the experimental group as the study progress, the observational pain scale C-PAINAD will also be completed by an independent pain observer, who will be blinded to the study’s hypotheses, the allocation of participants to the experimental/control conditions, and their total pain treatment consumption. As mentioned, the pain assessment will be conducted weekly during the 16-week study period (baseline assessment for 4 weeks and Protocol implementation for 12 weeks) in both the control and experimental homes. Participants will perform the standardized exercise programme while the pain observer is assessing their pain. In previous studies, the standardized exercise programme successfully triggered pain-related behavioral responses [32,33]. The exercise programme will include a set of passive range of motion (ROM) exercises involving the movement of all major joints. Each ROM will be repeated 10 times or moved to the point of resistance and held for 10 seconds. The participants will then be asked to perform a set of active motions that include changing position from lying to sitting, from sitting to standing, and then from standing to walking. The design of this standardized exercise programme was based on a literature review and followed consultation with a physiotherapist and a nurse with long-term care experience. This exercise programme is similar to the daily stretching exercises performed by physiotherapists in care homes. It helps older people retain joint flexibility and avoid joint stiffness. It was specially designed and has been used to evaluate the psychometric properties of four observational pain scales, including PAINAD [34]. It is believed that if participants suffer from pain under routine nursing care activities, this exercise programme will generate a level of pain similar to that experienced by the participants. This exercise will be performed by another well-trained RA who will be blinded to the study hypothesis and group allocation.

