### Intervention fidelity and training of independent pain observer/research assistant

Across the intervention period, daily to weekly visits by research personnel will be arranged for each care home during the 12-week period. Particularly during the first 2 weeks of the Protocol implementation period, a member of the research team will visit the care homes daily to ensure the smooth implementation of the Protocol. If staff have difficulty following the Protocol, meetings will be arranged to answer their concerns.

An independent pain observer will be trained by JL on how to use the C-PAINAD. She will also practise pain assessment using the C-PAINAD with various clinical vignettes. On-site practice will also be arranged. An acceptable inter-rater reliability (ICC = 0.9) will be established by comparing the pain scores rated by the observers with those rated by JL, who is experienced in using the C-PAINAD. JL will also instruct and evaluate the use of all instruments by the RAs. Monthly quality control meetings will be arranged with all research personnel in this study. The inter-rater reliability between the pain observer and JL will be checked at least monthly throughout the entire study period.

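### Bedside signs used only in experimental homes, and to a lesser degree joint monthly meetings, can show the pain observer which arm a home is in, so the stated blinding of C-PAINAD is not secured

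*Protocol article*

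**What the plan says.** The trial is described as single-blinded. The section on the independent pain observer states that this person is "blinded to the study’s hypotheses, the allocation of participants to the experimental/control conditions, and their total pain treatment consumption". It says the same of hypothesis and allocation for the assistant who leads the exercises. The Blinding section repeats the claim for the two assistants who collect all outcome data. The reason given for an independent observer is that "possible expectancy bias may develop among staff in the experimental group as the study progress".

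Four other parts of the article bear on this claim:

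- **Signs.** The pain-relieving interventions for experimental homes include this step: "Signs will be placed at bedsides to remind caregivers to take great care while conducting nursing activities". It belongs to the caregiving guidelines, whose trigger is "The guidelines should be implemented when the C-PAINAD score >1".
- **Sessions.** The observer rates C-PAINAD weekly in control and experimental homes, over 4 baseline weeks and 12 implementation weeks. Residents first have passive joint movements, then active motions: "changing position from lying to sitting, from sitting to standing, and then from standing to walking".
- **Allocation.** Under Randomization and allocation concealment, each home is a single unit with 15 to 16 participants.
- **Meetings.** The fidelity section says "Monthly quality control meetings will be arranged with all research personnel in this study". The same section describes team members who visit homes to support implementation.

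**The concern.** C-PAINAD is scored by judging breathing, vocalization, facial expression, body language and consolability. It is the outcome for the second research objective and the one that depends most on the rater. The independent observer is there to keep expectation out of those scores, which works only while she does not know the arm.

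The article gives her a way to find out. The signs are a visible feature described for one arm only. She sees each home before they could appear and afterwards, so a change can be noticed as well as a difference between homes. With home-level allocation, a cue at a single bed carries over to every resident there.

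If she does infer the arm and her scoring moves with it, part or all of a small difference in C-PAINAD could come from the rating and not from the residents' pain.

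**Working it through.** The plan gives no figure on this point, so there is none to reproduce. The check has two parts: setting the provisions side by side, and an illustration of what an assumed rating shift would do.

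**1. Could the observer meet the cue?**

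- *How common are signs likely to be?* The guidelines apply above a C-PAINAD score of 1. In the pilot (Background), "The mean pain score of the 30 residents decreased slightly from 2.87 (SD 1.30) at week 1 to 2.57 (SD 1.32) at week 8". The pilot mean lies (2.87 − 1)/1.30 = 1.44 SD above that threshold at week 1 and (2.57 − 1)/1.32 = 1.19 SD above it at week 8. If trial residents resemble pilot residents, signs would be common.
- *When?* The Protocol runs in weeks 5 to 16 and the observer attends in weeks 1 to 16. She has 4 weekly visits before signs are due and 12 afterwards.
- *Where?* The active motions start from lying and no assessment room is named. A session at the bed is plausible but is an inference.
- *How far does one cue reach?* One home is one unit, so it reaches all 15 to 16 participants.
- *Is there a stated shield?* The article does not say that signs are covered, that control homes have matching signs, or that sessions take place away from the bed. Table 1 also requires a pain chart for Protocol participants, and the article does not say where it is kept.

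**2. Could the meetings disclose allocation?**

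All research personnel attend. That covers the blinded assistants, the principal investigator and the team members who support implementation. The agenda is not given. The route is open, but nothing says it is used.

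**3. What would a rating shift do?**

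The documents give no size for such a shift, so the values below are assumptions. The inputs are 61 per group, 15% drop-out and a variance inflation factor of 1.31 (Sample size), pilot SDs of 1.30 and 1.32 (Background), and a two-sided 5% test.

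- Effective number per group: 61 × 0.85 / 1.31 = 39.6.
- Standard error of the difference: SD × √(2/39.6), which is 0.292 for SD 1.30 and 0.297 for SD 1.32.
- With no true effect and an average shift b between arms, the rejection probability is Φ(b/SE − 1.96) + Φ(−b/SE − 1.96).

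| Assumed shift b (points) | SD 1.30 | SD 1.32 |
|---|---|---|
| 0 | 5.0% | 5.0% |
| 0.1 | 6.4% | 6.3% |
| 0.2 | 10.5% | 10.3% |
| 0.3 | 17.7% | 17.3% |
| 0.4 | 27.8% | 27.1% |

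For scale, the pilot change was 2.87 − 2.57 = 0.3 points, or 0.3/1.31 = 0.23 SD. The planning effect of 0.4 SD is 0.4 × 1.30 = 0.52 to 0.4 × 1.32 = 0.53 points.

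This is a normal approximation to one comparison of means. It ignores the weekly repeats and the small number of homes, so it indicates the order of size only.

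**The case against.** The strongest reply is that a cue is being treated as a disclosure. Much of it is right:

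- The article says neither where sessions take place nor what the signs say. Passive exercises come before the lying-to-sitting motion, and the programme is likened to physiotherapists' routine stretching, so a therapy area also fits the text.
- The observer is blinded to the hypotheses and to treatment consumption as well as to allocation. A reminder to take care does not tell her which direction is hoped for, and any shift could go either way.
- Four workshops are held in both arms, so training activity does not mark the arm.
- The pilot change used for scale was uncontrolled and not statistically significant, and it is smaller than the planning effect.

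A reader might infer more than the documents support. C-PAINAD is not the only outcome collected by blinded staff, since the assistant who gathers MQS III scores and non-pharmacological treatment records is also declared blind. The meetings are not shown to disclose allocation. The observer's reliability checks against the principal investigator, at least monthly, are weak evidence of unblinding: that person works with both arms, and nothing says the arm is shared.

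A further reply is that such detail belongs in an operations manual, which an article may leave out. That would answer a complaint about a missing detail. Here the article itself states both the blinding claim and an arm-specific visible feature that works against it, and following the text as written puts the claim at risk.

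**Conclusion.** The concern holds in limited form. The plan claims allocation blinding for a subjective rating, describes a visible cue for experimental homes only, sends the observer into every home before and after that cue is due, and states nothing to keep her from it. Home-level allocation makes a single recognition enough for a whole home. The joint meetings are a second, weaker route.

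It would be tempting to conclude that the observer is unblinded and that C-PAINAD is in effect an open-label rating. The documents do not support that. Bedside sessions, recognisable signs and disclosure at meetings are all inferences, and blinding to hypotheses and treatment consumption gives partial protection even if the arm is guessed. The accurate conclusion is that the blinding is not secured.

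The size of any bias is unknown. If the arm were inferred and ratings shifted by 0.2 to 0.3 points on average, a test with no true effect would reject in about 10% to 18% of trials instead of 5%. A shift of 0.1 would hardly matter (about 6%). These figures rest wholly on the assumed shift and on the pilot SDs. The point concerns C-PAINAD. The two treatment-use outcomes come from records and depend less on the assessor's judgement.

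**What to change.** State in the protocol that, in all homes, observer sessions are held where signs and pain charts cannot be seen, either with these covered for the session or away from the bedside. Using one rule in both arms keeps the procedure itself from becoming a cue. Signs go back in view afterwards, and no treatment rule changes.

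Hold separate quality-control meetings for the blinded assistants, or bar allocation and implementation matters from joint ones.

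As an optional check, record the observer's guess of each home's allocation at the end, so that the success of blinding can be reported.

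The cost is protocol wording and a few minutes of staff time per weekly session, since home staff must cover and restore the signs or residents must be brought elsewhere. Separate meetings add a little organisation. The article reports that homes are still being recruited, so the change can be made before implementation begins.

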**Table 2 T2:** **Approaches to reducing the pain related to caregiving**[31]**]**

**Timely warnings**	- Place grab bars, transfer poles, and bed canes to assist with transfer and aid in self-directed care.
- Before a potentially painful movement or activity, give a warning, such as ‘I’m going to move your feet and put on your socks. Are you ready?’	
	- Brace painful knees during transfers.
	- Use a non-skid mat at the bedside to prevent sliding during transfers.
- Allow the resident to prepare for the action or movement.	- If the patient appears to be in pain, assess the usual transfer method for alternative, more comfortable ways of transferring. For example, beginning with two people, try the ‘carry transfer’ technique or use a mechanical lift.
- Wait for the resident to give permission (if she or he is able) before beginning the task.	
	- Evaluate the possibility of raising low beds from the floor to reduce pain associated with transfers, using a winged mattress to reduce the risk of falling.
	- Request an occupational therapy consultation for individualized techniques for transfers from low beds.
**Movement in bed**	
- Do not pull on arms when rolling or moving a resident in bed. Instead, grasp shoulders and hips, using a ‘log-roll’ technique to keep the body in proper alignment.	
- Use draw sheets to roll the patient from side to side rather than pulling and pushing on various parts of the body.	
**Transferring**	**Seating and positioning**
- If a patient has insufficient upper-body strength, raise the head of the bed and help the patient onto her or his side before bringing her or him to a sitting position.	- Get an individualized wheelchair assessment from a physical or occupational therapist.
	- Ensure that footrests are fitted to the patient.
- Do not pull on the patient’s neck when moving or transferring.	- Pad areas of wheelchairs that cause pressure.
	- Evaluate comfort of wheelchair cushions; provide comfortable inserts.
- Allow a patient time at the edge of the bed to get her or his bearings before completing the transfer.	
	- Adjust tilt-in-space wheelchairs every 1 to 2 hours to relieve pressure and change position.
- Raise electric beds high enough that legs are bent at the knee at slightly more than 90° to assist patients in coming to a standing position.	
	- Provide a variety of seating options throughout the day; avoid using ‘geri-chairs’ which lack support and do not offer a functional position.
- Make sure the patient’s feet are touching the floor before transferring from bed to chair, to allow the patient to bear as much weight as possible.	

